# Effectiveness of cognitive behavioral therapy on kinesiophobia and oral health-related quality of life in patients with temporomandibular disorders, study protocol for a randomized controlled trial

**DOI:** 10.1097/MD.0000000000023295

**Published:** 2020-11-20

**Keywords:** cognitive behavioral therapy, kinesiophobia, oral health related quality of life, randomized controlled trial, temporomandibular disorders

## Abstract

**Background::**

Temporomandibular disorders (TMD) is a common physical and psychological disease in dental department. Pain and mandibular limitation are the main reasons for patients to seek oral treatment. However, the presence of kinesiophobia, patients often catastrophize pain, so as to avoid mandibular movement, which seriously affects their quality of life. Cognitive behavioral therapy (CBT) has significant improvements in reducing kinesiophobia and quality of life in musculoskeletal disease, but has not been proved in TMD patients. The study aims to apply CBT on kinesiophobia and oral health related quality of life (OHRQOL) in TMD patients.

**Methods::**

A total of 108 individuals between 18 and 65 years of age, who will be referred to the temporomandibular joint clinic of Stomatology Hospital of Tianjin Medical University in china will be randomized into 2 treatment arms. The control group will receive a conventional treatment, whereas the experiment group will receive CBT on the basis of the control group. The primary outcomes will be the kinesiophobia and OHRQOL, and will be measured by the Tampa scale for kinesiophobia for patients with Temporomandibular Disorders (TSK-TMD) and the Oral Health Impact Scale for patients with temporomandibular disorders (OHIP-TMDs), the secondary outcomes will be pain intensity measured by Numerical Rating Scale (NRS), pain catastrophizing measured by Pain Catastrophizing Scale (PCS), anxiety and depression measured by Hospital Anxiety and Depression Scale (HADS), and self-efficacy measured by General Self-Efficacy Scale (GSES).

**Discussion::**

This study protocol reported a randomized controlled trial which aimed at assessing the effectiveness of the CBT versus conventional treatment with TMD.

**Trial registration::**

Registered in the Chinese Clinical Trial Registration Center with the number ChiCTR2000038573. Registered 24 September 2020.

## Introduction

1

Temporomandibular disorders (TMD), is a general term for a class of diseases that involve temporomandibular joint (TMJ) and the corresponding soft tissues, which are characterized by muscle pain, abnormal mandibular function accompanied by dysfunction and abnormal joint sounds.^[1]^ Approximately 14.9% to 17.9% of the Chinese population suffered from TMD, and approximately 50% experience chronic pain.^[2,3]^ The early symptoms of TMD are relatively mild and easy to ignore, whereas the later symptoms are more severe, including restricted opening of the mouth, obvious pain, inability to chew normally, headaches, insomnia, dizziness, tinnitus, shoulder and neck pain, neurasthenia, irritability and other mental symptoms, which seriously affect daily life and physiological functions.^[4]^ The etiology of TMD is complex, which is believed to be the result of a combination of multiple factors. Many studies show that mental and psychological factors are the main factors that cause TMD, whereas pain intensity and fear of mandibular joint movement are the major reasons for TMD patients to seek oral treatment.^[5–7]^

Kinesiophobia, describes an excessive, irrational fear of physical activity that stems from susceptibility to painful injuries.^[8]^ Evidence shows that TMD has a pain amplification mechanism, patients are more sensitive to pain and the pain perception disappears for a longer time compared with the general population, and they take the necessary action to control pain and discomfort when experience it.^[9]^ For TMD patients, controlling the movement of the mandibular joint prevents the discomfort, therefore they avoid movement of the mandibular joint. The avoiding behaviors will be strengthened when the discomfort recurs, which is called to avoid positive feedback.^[10]^ This high level of vigilance against pain limits normal mandibular joint activities, which has a serious impact on the physical and mental health of patients.^[11]^ In addition to pain, Knapik believes that kinesiophobia may also be the fear of fatigue and physical symptoms, the fear of physical and mental discomfort, or the incoordination between the actual needs of the individual and the athletic ability.^[12]^

Physical activity and rehabilitation exercise are of great significance to functional recovery for chronic musculoskeletal diseases, such as chronic low back pain, fibromyalgia, knee pain, and other diseases.^[13]^ Functional recovery is the long-term treatment goal, besides the treatment of the injury, after bones and joints injury and the loss of limb function.^[14]^ Early exercise can increase blood circulation of the injured limb, restore the articular surface mobility, reduce joint stiffness and muscle atrophy.^[15]^ However, evidence show that kinesiophobia is an important predictor of disability in patients with acute or chronic low back pain,^[13]^ fibromyalgia,^[16]^ osteoarthritis,^[15]^ neck pain and other chronic musculoskeletal,^[17]^ leading to the occurrence of disuse syndrome.^[18]^

TMD have many similarities to chronic musculoskeletal diseases. Pain is the main complaint, but the affected area is limited to the maxillofacial region. Joint noise is a milder symptom in the early stage. In severe cases, the joint locking or jamming will appear, and patients will have total inability to open their mouth eventually.^[19]^ However, the incidence of joint locking is only 15%, most patients suffer from short-term function limitation. Conservative treatments are commonly used for TMD clinically. Among these therapies, mandibular exercise significantly relieve the disease symptoms.^[20]^ However, patients may avoid mandibular movement due to fear of pain, fatigue of the mandibular joint, and lack of correct coping ability. Long-term avoidance of joint movement causes positive feedback loops, This may affect the patient's eating, pronunciation, aggravating anxiety and depression, which has a serious impact on the patient's quality of life.^[21]^

Oral health-related quality of life (OHRQOL) is a comprehensive evaluation index that reflects the impact of oral diseases and prevention on patients’ physical, psychological, and social functions.^[22,23]^ Clarifying the OHRQOL is conducive to the choice of treatment, the detection of patient prognosis, as well as tracking oral risk factors.^[24,25]^ At present, the most common psychological problems that have been proved to affect TMD patients are anxiety, depression, and stress, but kinesiophobia didn’t get much attention.^[26,27]^ However, in the early stage of the research, the research group investigated the level of kinesiophobia and oral health-related quality of life (OHRQOL) in chronic painful TMD patients who were treated at Stomatological Hospital of Tianjin Medical University. The results show that the level of kinesiophobia in TMD patients is higher than the Korean TMD patients reported by Korean scholars.^[28]^ Kinesiophobia adversely affects patients’ oral function, psychophysiological status, and social activities, which can explain 75.2% of the variance in OHRQOL.^[29]^ Therefore, how to reduce kinesiophobia and improve the OHRQOL are the essential issues that should be considered in managing TMD.

Cognitive-behavioral therapy (CBT) refers to a psychological treatment to correct bad cognition by changing patients’ thinking, belief, and behavior, and to eliminate bad emotions and negative behaviors.^[30]^ It is characterized by integrity, initiative, enthusiasm, and a short course of treatment, and is suitable for patients without mental disorders.^[30,31]^ Studies show that CBT not only identifies and corrects errors in patients with automatic thinking and bad cognitive behavior, and reduces the patient's kinesiophobia, but also helps to enhance the patient's self-efficacy, alleviates anxiety and depression, improves physical activity and quality of life.^[32–35]^

However, to our knowledge, no previous studies have examined CBT for kinesiophobia in TMD patients. The purpose of this study is to apply CBT to TMD patients. Kinesiophobia and OHRQOL will be taken as the main outcomes, whereas pain intensity, pain catastrophizing, anxiety and depression, and self-efficacy will be taken as the secondary outcomes to explore the effects of CBT.

## Methods

2

### Study design

2.1

This study is a single blind randomized controlled trial with two parallel groups. This protocol was reported based on Standard Protocol Items: recommendations for Interventional Trials (SPIRIT) guidelines.^[36]^

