#### Experiment group

2.6.2

The experimental group will perform CBT on the basis of the control group. The CBT in this study will mainly be implemented by therapeutic meetings. The intervention times are the first visit and the second visit (the first and second weeks after the first visit), a total of three times, each meeting last about 30 minutes. The specific intervention steps and methods are as follows:

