### Patient recruitment

2.12

Recruitment for the study will begin in November 2020 and is expected to be completed in January 2020. Information about the purpose and process of the study will be provided orally by the researcher. The participants can ask questions or doubts about any aspect of the study. The investigator will provide participants with a guarantee of data confidentiality. The informed consent includes the background and purpose of the study, therapeutic interventions, research findings, and expected strengths and weaknesses.

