### Randomization and blinding

2.13

The randomization of this study will be carried out by researchers who are not involved in recruitment. Participants will be grouped by the random number table method. Items assigned will be hidden and sealed in an opaque envelope in sequential numbered order. Participants will be randomly assigned to experiment group and control group. Before random allocation, they don’t know which treatment they would receive (Fig. 2).

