Diagnostic and statistical manual of mental disorders (DSM)^[58]^ and international classification of diseases (ICD)^[59]^ has been recommended for psychiatric diagnosis. These manuals may contribute to the diagnosis of Axis II in TMD patients and the implementation of psychosocial interventions. However, the diagnostic criteria for Axis II are not widely used in China, and there are no clinical studies providing psychosocial treatment for TMD patients. However, the importance of axis II diagnosis and psychosomatic intervention should be recognized in managing TMD pain. Therefore, the clinical collaboration between TMD specialists and psychologists is essential to manage TMD.

It should be mentioned that the study has some limitations. First, this study will be only conducted in a specialized stomatological hospital with limited sample size, large sample size and multi-center randomized controlled trials can be carried out to verify the reliability of our study. Second, the outcomes of the study are mainly measured by self-report questionnaires. However, the differences generated by objective indicators are relatively small. Third, the study will only conduct CBT program, further research could combine exercise intervention, mindfulness intervention and other multi-component intervention treatment to explore the effects on kinesiophobia and OHRQOL in patients with TMD.

The study is a randomized controlled trial that aims to explore the CBT on kinesiophobia and OHRQOL in patients with TMD. The research results would provide supplements for the treatment and management of kinesiophobia, as well as provide evidence for controversial topics in TMD patients with CBT treatment.

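### The trial is called single blind, but the measures described are allocation concealment, and participants who will know their arm score every listed outcome

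*Protocol article*

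**What the plan says.** **The label.** Section 2.1 (Study design) states: "This study is a single blind randomized controlled trial with two parallel groups". The text of the article does not name the blinded party there or elsewhere.

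**The method.** Section 2.13 (Randomization and blinding) uses a random number table and adds three measures:
- who randomizes: "The randomization of this study will be carried out by researchers who are not involved in recruitment";
- envelopes: "Items assigned will be hidden and sealed in an opaque envelope in sequential numbered order";
- what participants know: "Before random allocation, they don’t know which treatment they would receive".

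**The comparison.** The abstract states: "The control group will receive a conventional treatment, whereas the experiment group will receive CBT on the basis of the control group". Section 2.6.2 adds: "The CBT in this study will mainly be implemented by therapeutic meetings". There are three meetings of about 30 minutes each, and two members of the intervention team carry out the intervention.

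**The outcomes.** Sections 2.8 and 2.9 list two primary scales (TSK-TMD, OHIP-TMDs) and four secondary instruments (NRS, GSES, PCS, HADS). Section 2.14 has the participants complete the questionnaires, and section 2.9 has patients rate their own pain. The Discussion gives as a limitation that "the outcomes of the study are mainly measured by self-report questionnaires", without mentioning that those reporting will know their arm.

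**The concern.** Concealment and blinding protect against different things. Concealment keeps the next assignment from being foreseen, so that enrolment cannot be steered. It has done its work once the envelope is opened. Blinding keeps knowledge of the arm out of treatment, reporting and measurement after that moment. Section 2.13 describes the first and is offered in support of a claim about the second.

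A reader told that a trial is single blind will usually assume that either the participants or the outcome assessors do not know the arm. In this trial those are the same people, because every listed outcome is self-reported. If they know their arm, the main source of measurement bias is open, and the label leads the reader to under-rate it. What is at stake is how much weight a between-group difference in kinesiophobia or oral health-related quality of life can bear.

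**Working it through.** No calculation decides this point. It rests on setting the article's own statements side by side.

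1. **Is anything in section 2.13 blinding?** The random number table is sequence generation. Randomizers separate from recruiters, and opaque sequentially numbered envelopes, are allocation concealment. Participants' ignorance of the arm is stated only for the time before allocation, which is equally true of any open-label trial with concealed allocation. Nothing describes masking of participants, deliverers, data collectors or analysts afterwards.

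2. **Can participants stay unaware of their arm?** The control arm receives conventional treatment (section 2.6.1). The experiment arm receives the same plus three face-to-face meetings, and the WeChat follow-up out to six months is described only for that arm (section 2.6.2, Table 1). No sham or attention control is described. On consent, section 2.12 says: "The informed consent includes the background and purpose of the study, therapeutic interventions, research findings, and expected strengths and weaknesses". A participant told what the interventions are can recognise whether the CBT meetings are taking place. The article does not state outright that participants are unblinded; this follows from the design.

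3. **Can the deliverers stay unaware?** No. They conduct the meetings.

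4. **Who scores the outcomes?**

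| Role | Instrument | Scored by |
|---|---|---|
| Primary | TSK-TMD | participant |
| Primary | OHIP-TMDs | participant |
| Secondary | NRS | participant |
| Secondary | PCS | participant |
| Secondary | HADS | participant |
| Secondary | GSES | participant |

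   That is 2 of 2 primary and 4 of 4 secondary instruments. The clinical measurements in section 2.10 come from the case book, but they are not listed as outcomes.

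5. **Would a masked analyst or data handler supply the missing protection?** Not for this bias. A score already given by someone who knows the arm is not changed by who enters or analyses it.

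6. **Can the bias be sized?** Two quantities would be needed, and the article gives neither. One is the reporting shift. The other is the between-group difference the trial was designed to detect: section 2.11 gives an SD of 6.96, 90% power, a 0.05 level and 90 patients, but no difference. Back-solving with 45 per arm and the normal approximation gives
   - two-sided: 6.96 × (1.960 + 1.282) × √(2/45) ≈ 4.76 points;
   - one-sided: 6.96 × (1.645 + 1.282) × √(2/45) ≈ 4.29 points.

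   Any ratio of shift to difference would divide an assumed number by a conditional one, so none is offered as a finding.

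**The case against.** **The blinded party could be someone else.** Section 2.1 does not say that participants are blinded. A masked analyst or data handler would fit the words single blind, the full protocol is not at hand, and Figures 1 and 2 are not shown. This stands as far as it goes. A reader might infer that the trial has no blinding of any kind, and the documents do not support that; they show only that none is described. It does not rescue the outcome assessment, for the reason in step 5.

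**An article may condense.** True of detail. Here, however, the article asserts a design property and supports it, under a heading that includes blinding, with a measure that is not blinding. That is a wrong description, not an omitted one.

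**Open CBT trials are normal.** Participants cannot realistically be blinded to added meetings, and fear of movement and quality of life are inherently self-reported. This stands. The open design is not the fault; the label is.

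**CBT is meant to change the beliefs that TSK-TMD asks about.** A reader might treat a lower score after sessions that correct fear beliefs as an artefact. The documents do not support that: changing those beliefs is the stated aim, so a lower score may be the treatment effect. Answering to please the team is a separate possibility, and the design cannot distinguish the two.

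**Self-report is already acknowledged.** It is, in the Discussion, but without any link to knowledge of the arm.

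**Nothing says the deliverers handle questionnaires.** Correct. Keeping them apart is a precaution, not the correction of a stated practice.

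**Conclusion.** The concern holds in this form: the article calls the trial single blind without naming who is blinded, the supporting section describes only allocation concealment, and outcome assessment as described is not blinded. All six listed instruments are affected. The conclusion assumes that no sham or attention control exists beyond what the article describes, and that participants recognise their arm from the meetings they do or do not attend.

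Knowledge of the arm may bias the self-reports, and the plausible direction is towards CBT. A reader might go further and say that every outcome is pushed in favour of CBT, or quote the bias as a share of the target difference. The documents establish neither the certainty nor a size.

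This should be fixed but is not critical. The essential correction is one of description and changes no outcome, sample size or test.

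**What to change.** 1. In sections 2.1 and 2.13, describe the trial as open-label for participants and treatment staff, with concealed allocation. Name any party who is in fact masked, for example the data-entry person or the analyst, and say how.
2. Have questionnaires completed away from the two CBT deliverers, and neither collected nor entered by them. Someone outside the five-member intervention team would be preferable, because section 2.6.2 has its members share participants' progress with each other.
3. Enter and analyse the data under coded arm labels until the primary analysis is locked.
4. Extend the self-report limitation in the Discussion to say that both primary outcomes are reported by participants who know their arm, and carry that caveat into their interpretation.

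The registry record is not at hand; the sponsor should check that it matches the corrected description.

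**Cost.** A less favourable design label and some reassignment of questionnaire handling. Steps 2 and 3 limit bias from staff and analysts. They do not remove reporting bias at the level of the participant, which is why step 4 is needed.

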### Study setting

2.2

The study will be conducted at the TMJ clinic of the Stomatological Hospital of Tianjin Medical University in Tianjin, China. The participants will be informed the procedures, risks, benefits and the consent form, which will be conducted in accordance with the schedule described in Figure 1.

**Figure 1 F1:**
[figure not shown]
Standard protocol items: recommendations for Interventional Trials (SPIRIT) figure.

### Participants

2.3

The Research Diagnostic Criteria Axis I for Temporomandibular Disorders (RDC/TMD-Axis I) will be adopted in the present study.^[37]^

### Inclusion criteria

2.4

To participate in the study individuals must conform the following inclusion criteria:

1.Patients who meet the RDC/TMD-Axis I and are diagnosed with TMD;2.Age between 18 and 65 years, can fill in the questionnaire independently and truthfully;3.The chief complaint is accompanied by ≥3 months pain;4.Voluntary participation research and fill in the informed consent form.

### Exclusion criteria

2.5

Conversely, the exclusion criteria are:

1.Patients who have recently suffered from acute and chronic pulpitis, acute and chronic apical periodontitis, or suffered head and facial trauma;2.Patients with a history of rheumatism and rheumatoid diseases;3.Patients with a history of mental illness and drug addiction;4.Patients with a history of heart and liver dysfunction or malignant tumors.

### Interventions

2.6

#### Control group

2.6.1

Conventional treatment will be delivered by one of the study dentist/TMD specialist. Usual treatment is conservative and typically include use of occlusal splints, non-steroidal anti-inflammatory medications, and patient education that comprise of passive and active range of mandibular movement exercises, modification of parafunctional and/or dietary habits and regular application of cold and heat packs.^[34]^ No attempt will be made to influence patient dental treatment.

#### Experiment group

2.6.2

The experimental group will perform CBT on the basis of the control group. The CBT in this study will mainly be implemented by therapeutic meetings. The intervention times are the first visit and the second visit (the first and second weeks after the first visit), a total of three times, each meeting last about 30 minutes. The specific intervention steps and methods are as follows:

1.Establish an intervention team (before intervention)The study will establish an intervention group to ensure the frequent implementation. The members of this team include 1 TMD specialist, 1 nursing director, 1 doctor student (major in oral rehabilitation), 2 master students (major in dental nursing). The team will brainstorm and discuss, and then develop a pamphlet for interventions, which mainly includes the concept and mechanism of kinesiophobia, the relationship between fear-avoidance model, mandibular exercise, the importance of mandibular joint exercise. The site where the intervention will be implemented is the waiting hall of the TMJ clinic. Two members of the team will conduct cognitive and behavioral interventions on the participants. The members of the team should summarize the progress of the intervention of the research object in time, and communicate with each other to make the intervention plan proceed frequently.2.Implementation of intervention measures (therapeutic meeting)Session 1 (the first intervention)The main task of this session is to establish a good communication relationship with the patient and cognitive assessment. The researcher will choose the appropriate language and communication skills to communicate with patients so that they could reduce the sense of distance and establish a good cooperative relationship with participants, and then we understand the level of kinesiophobia in patients as well as the recognition of mandibular rehabilitation exercises, and record the related factors of kinesiophobia. Once we identify the patient's negative thoughts, we should make corresponding health education. At the same time, patients will be asked to scan the QR code of WeChat APP to obtain knowledge about TMD. After this session, it is necessary to summarize and provide feedback to determine whether the researcher and the patient's understanding are consistent.Session 2 (the second intervention)First, the researchers will review the main content of the last meeting with the patient to understand their recent problems, so that they can prioritize the problems, and discuss, summarize and feedback on the important issues. Through the summary of the cognitive evaluation stage, the irrationality in thinking may be discovered by the researchers. For example, patients may have misconceptions such as “When I open my mouth, the pain will increase and the mouth will be painful”, “Joint exercises will cause joint deformities”, etc. Researchers should correct the patient's misconceptions in time, emphasizing that avoidance behavior can lead to joint capsule adhesion and long-term joint noise. In severe cases, it will be difficult to open the mouth and the pain will get worse. Early joint exercises are of great significance to restore mandibular function. Researchers should guide patients to divert attention and make positive changes, so that patients know that kinesiophobia is a problem to be solved rather than a decisive factor in life. By increasing the patient's confidence in overcoming the fear of exercise. At this stage, behavioral intervention can be used to reduce the patient's fear of exercise and relieve the patient's anxiety, depression and other unhealthy emotions.Session 3 (the third intervention)The task of the third stage is cognitive reconstruction. The researcher will draft a complete long-term plan for the patient by checking the completion of the patient's target task, as well as affirm the patient's progress to further enhance the understanding of kinesiophobia and improve the patient's compliance with mandibular joint exercises. Finally, they should encourage patients to continue to perform relaxation therapy based on education manuals or videos, and explain the patients’ misunderstandings. After the end of the intervention, the participants will be thanked for their participation and cooperation in the study and encouraged to make regular follow-up visits. If they have any questions, they can contact us by WeChat APP to establish follow-up relationship.Follow-up (1, 3, 6 months after the intervention)Researchers regularly push the knowledge about TMD and the protection of TMJ to patients through WeChat APP. During the first month of follow-up, it will push once a week, during the second to third months, once every two weeks, and once every month in the fourth to sixth month. The recovery of mandibular function will be asked regularly by researcher. The interventions will be described in Table 1.

**Table 1 T1:** Checklist of CBT on TMD patients.

Intervention process	Intervention time	Intervention goal	Intervention content
The first stage	First visit	To establish a good relationship with the patient; cognitive assessment	①Understand the degree of kinesiophobia of the patient; ②Understand the relevant risk factors that cause kinesiophobia in patients; ③Provide WeChat QR code to facilitate patients to obtain TMD related knowledge; ④Establish short-term and long-term exercise goals based on the patient's terrorism and cognitive and cultural level.
The second stage	One week after the first visit)	Review the last conversation and get the latest news of the patient; correct unreasonable cognition	①Discover unreasonable disease thinking and cognition, and promptly correct the patient's “wrong cognition of thinking about kinesiophobia”; ②Explain the benefits of early joint exercises to patients; ③Encourage patients to overcome their kinesiophobia and continue to accomplish their goals.
The third stage	Follow-up consultation	Cognitive reconstruction	①Check the completion of the patient's rehabilitation goals and improve the exercise plan; ②Check the patient's mastery of relaxation training, find out the existing problems and give corrections and guidance; ③Encourage patients to perform rehabilitation exercises according to health education manuals and videos.
Follow-up	1, 3, and 6 month after the end of the intervention		①Regularly push TMD-related knowledge and how to protect the TMJ to patients through WeChat groups; ②The patients were followed up once a week in the first month after the intervention, every two weeks in the second to third months, and once a month in the fourth to sixth months, and patients were regularly asked about the improvement of pain and the recovery of mandibular function.

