### Sample size calculation

2.11

The sample size of this trial was based on the kinesiophoia score. Based on the previous research results of our research group, the mean of kinesiophobia was 34.37, with a standard deviation (SD) of 6.96 points.^[29]^ To achieve 90% power with a significant level of 0.05, a minimum of 90 patients is needed. Considering the possibility of withdrawal and loss of follow-up, the sample size was expanded by 20%, and the final sample size was determined to be 108 participants, with 54 participants in the experiment group and 54 participants in the control group. Sample Size was performed by using PASS Software (version 14.0; NCSS Statistical Software, Kaysville, UT) (http://www.ncss.com/software/pass/).

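### CBT meetings are placed in the waiting hall of the only study clinic, with no described separation from control patients: an avoidable contamination and privacy risk

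*Protocol article*

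**What the plan says.** Section 2.2 names one TMJ clinic as the setting for the whole study, and Section 2.13 assigns individual participants to the two arms.

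For controls, Section 2.6.1 says: "Conventional treatment will be delivered by one of the study dentist/TMD specialist". Section 2.6.2 adds CBT to that same care in the experimental arm, as three meetings of about 30 minutes each. On where the meetings happen: "The site where the intervention will be implemented is the waiting hall of the TMJ clinic". On who prepares the material: "The members of this team include 1 TMD specialist, 1 nursing director", with three students completing the team. Two unnamed team members deliver the sessions.

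The CBT content, as set out in Section 2.6.2 and Table 1, includes a pamphlet, a WeChat QR code, spoken correction of mistaken beliefs, and later material sent through WeChat groups.

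Section 2.11 sizes the trial on the kinesiophobia score: "To achieve 90% power with a significant level of 0.05, a minimum of 90 patients is needed". This is raised by 20% to 108, with withdrawal and loss to follow-up as the only reason given.

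**The concern.** The place of delivery is a stated choice, not a detail left to a fuller document. In a single-clinic trial with individual randomisation, an open waiting area is where patients of both arms are most likely to cross. Much of this CBT is spoken or printed information about fear, avoidance and the value of early exercise, so some of it can be overheard, seen or passed on.

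Two things are at stake. First, if controls absorb part of the CBT content, the arms move closer together and the trial loses power. This cannot be undone afterwards, and a null result would be hard to interpret. Second, the first session depends on patients speaking candidly about their fears, and the second also addresses anxiety and depression. A public area does not favour that, and the intervention under test may be weaker for it.

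**Working it through.** **Could controls be exposed?** There is one clinic (2.2), individual allocation (2.13), conventional treatment for controls (2.6.1) and the same treatment plus CBT for the other arm (2.6.2). Both arms therefore attend this clinic, and a shared waiting hall is a close inference. If every CBT patient attends every meeting, there are 54 × 3 = 162 meetings, and 162 × 0.5 h = 81 hours of CBT in that hall.

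**Inputs for the illustration**
- From Section 2.11: "the mean of kinesiophobia was 34.37, with a standard deviation (SD) of 6.96 points"; 90% power; alpha 0.05 (sidedness not stated, two-sided assumed); 90 patients, i.e. 45 per arm; 54 per arm after enlargement.
- Not in the article: the target difference (back-solved below) and the leakage rate c (assumed).

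**The plan's own figure.** Only one mean and one SD are given, so the 90 cannot be reproduced forward. The enlargement does reproduce: 90 × 1.2 = 108. Solving backward with the normal approximation:

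difference = SD × (1.960 + 1.282) × √(2/n) = 6.96 × 3.242 × √(2/45) = 4.76 points

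The noncentral t gives 4.81 points. A one-sided test would imply 4.29.

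**Dilution.** Let the difference shrink to 4.76 × (1 − c). Then

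power = Φ[ 4.76(1 − c) / (6.96 √(2/n)) − 1.960 ]

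Worked case, c = 10%, n = 45: the difference is 4.28, the standard error is 6.96 × √(2/45) = 1.467, and 4.28/1.467 − 1.960 = 0.958, so power is 83%.

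| Assumed dilution c | Difference (points) | Power, 45 per arm | Power, 54 per arm | Evaluable per arm for 90% |
|---|---|---|---|---|
| 0% | 4.76 | 90% | 94% | 45 |
| 5% | 4.52 | 87% | 92% | 50 |
| 10% | 4.28 | 83% | 89% | 56 |
| 20% | 3.81 | 74% | 81% | 71 |
| 30% | 3.33 | 62% | 70% | 92 |

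The noncentral t gives the same percentages at 10%, 20% and 30%. Under a one-sided test, 45 per arm gives 84% at 10% and 76% at 20%.

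In this approximation the difference and the SD cancel. The power column depends only on c and on taking the claim of 90% power at 45 per arm at face value.

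**The case against.** The strongest reply is that nothing here shows contamination will occur. The article does not say that controls are present during sessions, that sessions can be overheard, or that the pamphlet is on display. The CBT is largely individual: an assessment, correction of that patient's own beliefs, personal goals and progress checks. Overheard fragments may transfer little of it, so the higher dilution rates may be hard to credit. The planned analysis is also repeated-measures over four time points, and a two-sample calculation need not represent its power. All of this stands, and it is why the figures are an illustration and not an estimate.

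The direction is not certain either. Controls who see others receiving something extra might rate themselves worse or withdraw, which would bias the comparison the other way. No net effect can be derived from the article.

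Three stronger readings are tempting, and the article does not support them:
- **The same specialist treats both arms.** The CBT team includes a TMD specialist, and controls are treated by a study dentist or TMD specialist. The text neither states nor excludes that this is one person, and it does not say that the specialist is one of the two who deliver CBT. Overlap is a possibility only.
- **Exercise advice given to controls is contamination.** It is part of conventional treatment and so common to both arms by design.
- **The waiting hall contradicts the confidentiality promise.** Section 2.12 says: "The investigator will provide participants with a guarantee of data confidentiality". That concerns data, and Section 2.14 carries it out through concealed names and encrypted storage. It promises nothing about where conversations take place. Privacy is a fair practical concern, not a contradiction.

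What the reply does not answer is that the location is fixed in the text and no separation of place or material accompanies it.

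**Conclusion.** The concern holds as an avoidable risk, not as a demonstrated loss. The protocol puts the CBT meetings in an open area of the only study clinic, which control patients very probably use, and describes no separation of place or material. The sample size makes no stated allowance for dilution.

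A reader might infer that the stated 90% power is already lost. The article does not support this: it gives no leakage rate and no target difference. Conditional on a back-solved difference of about 4.8 points and an assumed 10% to 20% dilution, power would be about 83% to 74% if 45 per arm are evaluable, and about 89% to 81% if all 54 are. With all 108 patients analysed, a 10% dilution would barely move power from the planned 90%.

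This is a cheap improvement worth making before recruitment, because contamination cannot be corrected later.

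**What to change.** 1. In Section 2.6.2, replace the waiting hall with a closed room of the clinic as the place for the CBT meetings.
2. State that the pamphlet, the QR code and WeChat group access go only to participants in the CBT arm.
3. At the month-6 assessment, ask control participants whether they saw or received any CBT material, and report the answer.

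The cost is booking a room and one extra question. The CBT content, its timing and the sample size stay as they are. The article gives no information on room availability, so the sponsor should confirm that a room can be had.
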